## Abstract

**Background:**

Diabetes mellitus is rapidly becoming one of the leading causes of morbidity and mortality worldwide. Preventive measures have become important, especially in the South Asian region and other parts of the world where diabetes is becoming increasingly prevalent. We postulate that a product containing amino acid lysine, micronutrient zinc and vitamin C will have beneficial effects on glycemic control and disease progression in patients with pre-diabetes and we aim to evaluate this hypothesis using a phase II/III randomized double-blind controlled clinical trial design.

**Methods/design:**

The study will be conducted as a randomized, double-blind, placebo-controlled clinical trial for a period of 6 months. The study has been approved by the Ethics Review Committee of Faculty of Medicine, University of Colombo, Sri Lanka. A total of 110 adults with pre-diabetes will be recruited for the study. They will be randomly assigned to the test and placebo groups on a 1:1 ratio. The test group will receive two tablets of Lysulin™ three times a day and the control group will receive identical placebo tablets. The study drugs will be double blinded to both investigators and subjects. The visits and the evaluations will be done as follows: screening (visit 0), 1 month (visit 1), 3 months (visit 2) and 6 months (visit 4). The primary outcome will be defined as change in glycemic control measured by HbA1c from baseline. Data will be analyzed using SPSS v16.

**Discussion:**

To our knowledge this is one of the first randomized controlled trials evaluating the effects of Lysulin™ (a combination of lysine, vitamin C and zinc) in pre-diabetes. This study will provide the necessary groundwork for future large-scale multicentered clinical trials. The result, positive or negative, should provide a step change in the evidence guiding current and future policies regarding management of pre-diabetes.

**Trial registration:**

Sri Lanka Clinical Trials Registry, SLCTR/2018/022. Registered on 13 July 2018. Study protocol version 2.0 (23 March 2018).

**Electronic supplementary material:**

The online version of this article (10.1186/s13063-019-3269-8) contains supplementary material, which is available to authorized users.

## Background

Diabetes mellitus is rapidly becoming one of the leading causes of morbidity and mortality worldwide [1]. In most regions of the world, diabetes has reached epidemic proportions, and in the South Asian region alone the projected increase in prevalence of diabetes is out of proportion to the estimated population increase. For instance, the total population will increase by 40% from 2000 to 2030, but the percentage of change in prevalence of diabetes is estimated to be 151% [2]. This has placed an increasing financial burden on health care systems around the world, and in the USA alone the total estimated cost of diagnosed diabetes in 2017 is $327 billion, including $237 million in direct medical costs [3]. An estimated 80% of the world’s population with diabetes are from developing countries, overwhelming their existing health care facilities [1]. Therefore, preventive measures have become important, especially in the South Asian region and other parts of the world where diabetes is becoming increasingly prevalent.

The causes of type 2 diabetes are multifactorial, and diet plays an important role in its incidence, severity and management [4]. Recent studies have demonstrated that numerous herbal and nutraceutical products have beneficial effects in patients by improving glucose and lipid metabolism, antioxidant status, disease progression and capillary function [5]. Lysulin™ is one such nutraceutical tablet manufactured in the USA which contains the essential amino acid lysine, micronutrient zinc and vitamin C as the active ingredients, together with other standard excipients (Lysulin Inc., San Diego, CA, USA) [6]. Lysulin™ is considered a dietary supplement under the Dietary Supplement Health and Education Act of 1994 of the US National Institute of Health (NIH) Food and Drug Regulatory Authority (FDA), as it contains only amino acids, vitamins and minerals [7].

Lysine is an essential amino acid that plays a major role in calcium absorption, building muscle protein, and the body’s production of hormones, enzymes and antibodies. It has also shown numerous beneficial effects in the treatment/prevention of diabetes and/or its complications in in-vivo animal and human studies. In diabetes-induced animal models, lysine has shown beneficial effect in lowering blood glucose as well as acting as an inhibitor of protein glycation [8]. Furthermore, the ability of lysine to reduce the formation of glycated proteins in diabetes-induced rats has also been shown to delay the appearance of the late pathologies associated with protein glycation [9]. Lysine is known to react with glucose, with the glycated amino acid being excreted in urine, and it has been shown to markedly attenuate the glucose response to ingested glucose without a change in insulin response in humans [10]. Furthermore, studies have shown that lysine reduces the formation of glycated proteins in diabetes-induced animal models [8]. Glycated proteins are known to be involved in the pathogenesis of several chronic diabetes complications, including nephropathy leading to chronic kidney disease, neuropathy and retinopathy, as well as in other macrovascular complications [11–13]. Hence, it is evident that lysine may have potentially beneficial effect on the reduction of blood glucose as well as on the progression of diabetes and its complications.

Zinc is involved in numerous metabolic pathways as a cofactor for more than 300 enzymes [7]. Insulin, which contains a variable number of zinc atoms, is stored in β-cells of the pancreas and released into the portal venous system at the time of β-cell degranulation. Studies have shown that zinc plays an important role for insulin action, carbohydrate and protein metabolism [10]. Zinc absorption is also known to be altered in patients with diabetes [14]. Numerous studies have shown that zinc supplementation improves glycemic control in patients with type 2 diabetes, with a resultant reduction in HbA1c of around 0.5% in pooled analysis [15]. A study conducted in Bangladesh demonstrated that individuals with pre-diabetes are also known to have lower serum zinc concentrations compared to those who are healthy [16]. Furthermore, a recently concluded clinical trial on patients with pre-diabetes demonstrated that zinc supplementation helps to reduce blood glucose and insulin resistance, while improving β-cell function [17]. Furthermore, disease progression to diabetes was also reduced and beneficial effects of supplementation were also noted on total and LDL cholesterol [17].

Ascorbic acid (vitamin C), an antioxidant vitamin, plays an important role in protecting free radical-induced damage. Previous study has shown a decrease in the basal vitamin C level in type 2 diabetes [18]. Vitamin C is structurally similar to glucose and can replace it in many chemical reactions, and thus is effective for prevention of nonenzymatic glycosylation of protein [19]. Furthermore, randomized controlled trials have shown that supplementation with vitamin C reduces blood glucose and serum lipids and improves HbA1c in type 2 diabetes [20]. Hence, we postulate that a product containing amino acid lysine, micronutrient zinc and vitamin C will have beneficial effects on glycemic control and disease progression in patients with pre-diabetes. The present study aims to evaluate this hypothesis using a phase II/III randomized double-blind controlled clinical trial design.

## Methods/design

This protocol was written following the Standard Protocol Items: Recommendations for Interventional trials (SPIRIT) checklist (see Additional file 1) [21]. The schedule of trial enrollment (SPIRIT figure), interventions and assessments is presented in Fig. 1.

**Fig. 1 Fig1:**
[figure not shown]
Summarized study schedule of enrolment, interventions and assessments in the clinical trial. ALT alanine aminotransferase, AST aspartate aminotransferase, FBG fasting blood glucose, FFQ Food Frequency Questionnaire, HDL high-density lipoprotein, OGTT oral glucose tolerance test

### Objectives and hypothesis

#### Hypotheses

Primary—the glycemic control of people with pre-diabetes who are treated with Lysulin™ tablets will be better than that of the control group.Secondary—progression to diabetes would be reduced and other related metabolic parameters (serum insulin, total cholesterol, triglyceride, HDL cholesterol, LDL cholesterol and blood pressure) will be improved in the treatment group in comparison to the control group.

#### Objectives

Primary—to evaluate the potential effects of Lysulin™ tablet supplementation on glycemic control and disease progression in patients with pre-diabetes.Secondary—to evaluate effects on serum lipids, anthropometric parameters, blood pressure and appetite, and also to study potential effects of regular administration of Lysulin™ tablets on liver and kidney function and the occurrence of self-reported side effects in patients with pre-diabetes.

### Study design

The study will be a phase II/III randomized, double-blind, placebo-controlled clinical trial. It will be conducted at the Nawaloka Hospital Research and Education Foundation (NHREF), Nawaloka Hospitals PLC, Colombo, Sri Lanka for a period of 6 months, assessing the effects of daily supplementation of Lysulin™ tablets in patients with pre-diabetes.

### Sample size

A total of 110 adults with pre-diabetes will be recruited for the study after a screening test confirming the presence of pre-diabetes as defined in ‘Population’ and further eligibility screening against other inclusion/exclusion criteria described in ‘Inclusion and exclusion criteria’. Summaries of previous studies of oral antidiabetic drugs suggest that they reduce HbA1a levels by 0.5–1.5% [22]. Numerous studies have shown that zinc supplementation reduces HbA1c by around 0.5% [15]. Hence, in the absence of preliminary studies in a comparable cohort, we assumed an HbA1c reduction of 0.5%. The number of patients required for determination of a 0.5% reduction of HbA1c in the treatment arm, in comparison with the placebo arm, at 80% power and 95% confidence interval with a drop-out rate of 20% was 108 patients. Hence, a total of 110 adults with diagnosed pre-diabetes will be recruited for the study. Subjects will be randomly and equally assigned into two groups (*n* = 55 each) and will receive either Lysulin™ oral tablet or an identical placebo daily for a period of 6 months. The formula used for sample size calculation was as follows:$$ N=\left[\left(1/{q}_1+1/{q}_2\right)\times {\left({Z}_{\alpha }+{Z}_{\beta}\right)}^2\right]/\left[{\left(E/S\right)}^2\right], $$

where *N* = sample size,

*q*_1_ = proportion of subjects in the treatment group (0.5),

*q*_2_ = proportion of subjects in the placebo group (0.5),

*Z*_*α*_ = critical value of the normal distribution at *α* (*α* = 0.05 and critical value = 1.96),

*Z*_*β*_ = critical value of the normal distribution at *β* (*β* = 0.2 and critical value = 0.84),

*E* = effect size (0.5% difference in HbA1c between the two groups) and

*S* = standard deviation of HbA1c in the population (in the absence of previous published studies on pre-diabetes in Sri Lanka that reported HbA1c values, this was assumed to be 0.82%, based on previous research conducted among patients with diabetes in Sri Lanka) [23].

### Population

Pre-diabetes is defined as the presence of fasting plasma glucose (FPG) between 100 and 125 mg/dl (impaired fasting glucose (IFG)), or 2-h post oral glucose tolerance test (OGTT) plasma glucose between 140 and 199 mg/dl (impaired glucose tolerance (IGT)), or both IFG and IGT, or an HbA1c value between 5.7 and 6.4% [24].

### Inclusion and exclusion criteria

#### Inclusion criteria

Age between 18 and 60 years.Screening test confirming the presence of pre-diabetes as defined in ‘Population’.

#### Exclusion criteria

On any other vitamin or mineral supplementations.Current use of a weight loss medicine or dietary modification.History of diabetes mellitus.Presently having acute diseases or other untreated illness requiring treatment.Impaired hepatic or renal functions.Patients with any malignancy or any other unrelated chronic illness.Patients with cardiac, liver or respiratory failure.Any condition in the opinion of the primary investigator that would contraindicate the patient’s participation.Allergy to any of the constituents of the tablets.Lactation, pregnancy or unwillingness to use an effective form of birth control for women of childbearing age.

#### Suspension criteria

Subject’s demand to discontinue the study.Serious adverse events or unusual changes in clinical test results.Principal investigator’s decision to terminate the study (low rates of compliance, complications or unable to sustain the study for various reasons).

### Randomization

Randomization for the parallel treatment arms will be carried out after checking the inclusion and exclusion criteria. The patients will be randomized in a 1:1 ratio according to the method of block randomization with a block size of 4. The population will be stratified at randomization based on age (< 30 years and ≥ 30 years) and gender to ensure equal distribution of these variables in the two arms. The randomization sequence would be generated using the SPSS statistical software package (version 14.0). Concealment of the allocation sequences will be done using sequentially numbered, opaque, sealed, color-coded envelopes. Eligibility assessment and enrolment will be done by one independent investigator, while another investigator will be involved in randomization. The investigator involved in randomization shall open the next respective color-coded envelope depending on the stratification and allocate the patient to the respective group (treatment or control). The treatment and control groups shall be designated as either ‘A’ or ‘B’ and this allocation shall be kept in a sealed envelope in a secure place during the course of the study. The manufacturer will be responsible for preparing the study medications designated either ‘A’ or ‘B’.

### Blinding

The investigators and patients would be blind to the treatment allocations. The medication will be delivered in similar packets and labels with its own sequence number. The allocation sequence number will be generated by one of the investigators not involved in managing patients. Envelopes containing a monthly supply containing Lysulin™ tablets or placebo will be prepared according to the randomization sequence and supplied to the patients by the principal investigator or research assistants when they are randomized to the trial.

### Interventions

The treatment drug will be a tablet containing amino acid lysine, elemental zinc and vitamin C as the active ingredient. All of the active ingredients are supplemented within the Recommended Daily Allowance (RDA) [25, 26]. The placebo tablet contains inactive ingredients (magnesium stearate and microcrystalline cellulose) and will be manufactured to have a similar appearance, shape, weight, taste, color, smell and texture. The drug manufacturing will be done at a US FDA-registered and GMP-certified manufacturing site in the USA. The manufacturer will be responsible for supplying the Lysulin™ and placebo tablets. However, the manufacturer/funding organization shall not be involved in any aspects related to the conduct of the study, including patient recruitment, follow-up and analysis of data.

Recruited subjects will receive either two tablets of Lysulin™ or placebo three times daily, taken 1 h before meals for a period of 6 months. Envelopes containing a monthly supply of Lysulin™ or placebo tablet will be prepared according to the randomization sequence and supplied to the patients. Participants in both groups will receive uniform advice about diet and physical activity, which are considered to be potential confounder variables affecting glycemic control.

### Study groups

The treatment group will receive Lysulin™ tablets (*n* = 55). The control group will receive placebo tablets (*n* = 55).

### Study period

The study will be for a period of 6 months and the visits and evaluations will be done as follows; screening (visit 0), 1 month (visit 1), 3 months (visit 2) and 6 months (visit 3) (Fig. 1).

### Outcomes

#### Primary outcome index

The primary outcome will be defined as the change in glycemic control measured by HbA1c from baseline.

#### Secondary outcomes

Change in FPG and OGTT plasma glucose from baseline.Development of diabetes during follow-up, as indicated by either FPG > 125 mg/dl and/or 2-h OGTT plasma glucose > 199 mg/dl and/or HbA1c > 6.5%, confirmed during follow-up visits [27].Change in lipid profile from baseline (total cholesterol, LDL, HDL and TAG).Change in insulin resistance from baseline. Insulin resistance would be measured by the Homeostasis Model of Assessment—Insulin Resistance (HOMA-IR) calculations based on fasting blood glucose and fasting serum insulin. Β-cell function would be evaluated in vivo (HOMA-B calculation) and in vitro.Change in anthropometric assessment such as body weight, height, body mass index (BMI), waist circumference (WC), hip circumference (HC) and waist:hip ratio (WHR) from baseline.Change in systolic blood pressure (SBP) and diastolic blood pressure (DBP) from baseline.

Level of physical activity (International Physical Activity Questionnaire (IPAQ) short form) and dietary intake (validated Food Frequency Questionnaire) would be assessed in both groups as they are confounding factors affecting glycemic control.

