#### Study schedule

Fasting blood glucose, 2-h OGTT blood glucose, serum insulin, the liver profile (AST, ALT, PT/INR) and the renal profile (blood urea and serum creatinine) will be measured at the 0,1, 3 and 6 months. In addition, the serum lipid profile (total cholesterol, triglycerides, LDL cholesterol, HDL cholesterol) and serum HbA_1_c would be measured at baseline, at 3 months and on completion of the study. The details of items which will be measured at every visit are described in Fig. 1.

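### The HbA1c limit for incident diabetes (> 6.5%) does not join the pre-diabetes range (to 6.4%), so a reading of 6.5% is not counted as a conversion

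*Protocol article*

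**What the plan says.** The Population section of the protocol article gives three numerical ranges for pre-diabetes, any one of which is enough:

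- fasting glucose: "fasting plasma glucose (FPG) between 100 and 125 mg/dl (impaired fasting glucose (IFG";
- 2-hour OGTT: "plasma glucose between 140 and 199 mg/dl (impaired glucose tolerance (IGT";
- HbA1c: "or an HbA1c value between 5.7 and 6.4" per cent.

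The Secondary outcomes section then counts a participant as having developed diabetes on "either FPG > 125 mg/dl and/or 2-h OGTT plasma glucose > 199 mg/dl and/or HbA1c > 6.5%, confirmed during follow-up visits". This is the only operational definition of progression in the article. The Study schedule section adds that HbA1c "would be measured at baseline, at 3 months and on completion of the study", while fasting and 2-hour glucose are taken at 0, 1, 3 and 6 months.

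**The concern.** Two of the three outcome limits start exactly where the matching pre-diabetes range stops, and the third does not. Because the two glucose limits in the same sentence are contiguous with their ranges, the HbA1c limit looks like a slip in the operator rather than a deliberate choice. No section of the article says how 6.5% is to be classed.

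Taken literally, the rule makes 6.5% a non-event on the HbA1c criterion, although by the protocol's own definition that reading has left the pre-diabetes range. Progression to diabetes is named in the secondary hypothesis and listed as a secondary outcome, and disease progression also appears in the primary objective. With 55 participants per arm and six months of follow-up, a few participants classed differently could change the event counts noticeably. If the mismatch is first noticed during the analysis, the choice between the two limits would be made with data in hand.

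**Working it through.** **Step 1. Does the limit enter the plan's own figure?** The only derived figure in the Sample size section is 108 patients. The inputs there are a difference of 0.5%, an SD of 0.82%, critical values of 1.96 and 0.84, equal allocation and 20% drop-out.

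- N = (1/0.5 + 1/0.5) × (1.96 + 0.84)² / (0.5/0.82)² = 84.3
- Per arm: 84.3 / 2 = 42.2, rounded up to 43, so 86 in total
- With drop-out: 86 / 0.8 = 107.5, rounded up to 108

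The stated 108 is reproduced. It rests on the mean change in HbA1c, and no diabetes cut-point enters it.

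**Step 2. Class each reportable value near the boundary.** The ranges come from Population and the limits from Secondary outcomes. Reporting units are taken as 1 mg/dl for glucose and 0.1% for HbA1c, as the limits are written.

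| Measure | Last pre-diabetes value | Next value up | First value counted as diabetes | Values in between |
|---|---|---|---|---|
| FPG (mg/dl) | 125 | 126 | 126 (> 125) | none |
| 2-h OGTT (mg/dl) | 199 | 200 | 200 (> 199) | none |
| HbA1c (%) | 6.4 | 6.5 | 6.6 (> 6.5) | 6.5 |

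Exactly one reportable HbA1c value falls between the two definitions. If the laboratory reports two decimals, the gap is every value above 6.40 up to and including 6.50.

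**Step 3. Direction.** Raising a limit from ≥ 6.5% to > 6.5% can only remove HbA1c conversions. The criteria are joined by and/or, so a participant is lost to the outcome only if HbA1c reads 6.5% and neither glucose criterion is met.

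**Step 4. Illustrative size.** The protocol gives no follow-up HbA1c distribution, so what follows is assumption. Take HbA1c at one visit as normal with mean 5.8, 6.0 or 6.2% and SD 0.3, 0.5 or 0.82%. The last SD is the sample-size value, which the protocol took from patients with diabetes. A reading of 6.5% covers true values from 6.45 to 6.55.

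- Share reading 6.5% = Φ((6.55 − mean)/SD) − Φ((6.45 − mean)/SD)
- Share of all readings of 6.5% or more = that quantity / [1 − Φ((6.45 − mean)/SD)]

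| Mean | SD | Reads 6.5% | Of 110 | As share of readings ≥ 6.5% |
|---|---|---|---|---|
| 5.8 | 0.3 | 0.89% | 1.0 | 59% |
| 5.8 | 0.5 | 3.00% | 3.3 | 31% |
| 5.8 | 0.82 | 3.38% | 3.7 | 16% |
| 6.0 | 0.3 | 3.34% | 3.7 | 50% |
| 6.0 | 0.5 | 4.84% | 5.3 | 26% |
| 6.0 | 0.82 | 4.04% | 4.4 | 14% |
| 6.2 | 0.3 | 8.07% | 8.9 | 40% |
| 6.2 | 0.5 | 6.66% | 7.3 | 22% |
| 6.2 | 0.82 | 4.55% | 5.0 | 12% |

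These counts are taken before any capture by FPG or OGTT. Under each assumed distribution, the number actually missed at that visit would be the same or smaller.

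**Step 5. After the change.** With ≥ 6.5%, 6.4% is pre-diabetes, 6.5% is diabetes and no reportable value is left over. The sample size stays at 108, rounded by the protocol to 110.

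**The case against.** The strongest reply is that little depends on this limit, and most of that reply stands. Development of diabetes is a secondary outcome. The primary outcome is change in HbA1c as a continuous measure. Both glucose tests are scheduled at every post-baseline visit where HbA1c is measured, so some participants at 6.5% will be counted through FPG or OGTT. The rule can also be applied as written: it yields a clear non-event at 6.5%, and the fault is that this disagrees with the Population section.

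The documents do not support four stronger readings that a reader might infer.

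- *That the limit favours one arm.* The same rule applies to both blinded arms, and nothing in the protocol points to a directional bias.
- *That 6.4% is a ceiling for entry, so everyone starts just below the gap.* The Population criteria are alternatives. A participant may enter on FPG or OGTT alone, and no separate upper HbA1c limit is set.
- *That most conversions fall at the borderline.* The protocol has no data on conversions or on follow-up HbA1c from which to say so.
- *That the requirement for confirmation at follow-up visits discards conversions first seen at month 6.* This needs the word to mean a repeat of the same test at a later scheduled visit. It can equally mean that the crossing is established at a visit, and the full protocol, which may give the procedure, is not shown.

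**Conclusion.** The inconsistency is certain on the text: the Population section stops pre-diabetes at HbA1c 6.4%, the Secondary outcomes section starts diabetes above 6.5%, and nothing else in the article reconciles them. The effect is an under-count of HbA1c-based conversions, limited to participants who read 6.5% and meet neither glucose criterion. The size of that loss cannot be derived from the documents. The illustration of about 1 to 9 of 110 participants at 6.5% rests on assumed normal distributions and one-decimal reporting, and does not allow for capture by glucose.

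The cost is some events and some precision in one secondary outcome. The primary analysis and the sample size are untouched. The point should be corrected because the trial would otherwise apply a limit at odds with its own definition, but it is not serious enough to hold up the trial.

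**What to change.** Reconcile the Population and Secondary outcomes sections so that the HbA1c outcome limit joins the pre-diabetes range as the two glucose limits do: write HbA1c ≥ 6.5%, which at one decimal is the same as > 6.4%. State the reporting precision in the same place, because the two forms differ if two decimals are used.

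This changes one line of an outcome definition. It needs no new measurements, leaves the sample size as it is, and does not affect the primary analysis. The Trial status section says that enrolment has not started, so the change can be made, dated and notified as a protocol amendment before any outcome is seen.
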